### Patient Selection

Patients who meet all of the following criteria are considered eligible to take part in the study: 1) chronic (>6 weeks) symptomatic HF despite stable, optimal drug therapy for HF and AF, 2) patients scheduled for and implanted with a cardiac resynchronization device with defibrillator backup according to current guidelines. 3) age 18 or above, or of legal age to give informed consent according to specific national regulations. Principal exclusion criteria include: 1) chronic or persistent atrial fibrillation refractory to medical or electrical therapy 2) valve disease, and/or patients with or who are likely to receive a mechanical tricuspid valve during the course of the study 3) patients who have undergone (or are scheduled to undergo) an intervention of atrial fibrillation ablation 4) cerebral vascular event or transient ischemic attack within 12 months of implantation which lead to significant impairment 5) life expectancy of less than 1 year due to other medical conditions 6) NYHA class IV. According to the listed criteria, patients are not selected on the basis of atrial arrhythmia recurrence, except for chronic/persistent AF.

### Interventions and Follow Up

After obtaining informed consent, patients' baseline data are collected, including demographic background and medical history. A clinical evaluation performed at the time of enrollment includes NYHA class assessment, an electrocardiogram, an echocardiogram and Qol assessment using the Minnesota-Living With Heart Failure questionnaire. During the three-month observation period before randomization, we collect data on the incidence of supraventricular arrhythmia and clinical events; deaths from any cause or chronic atrial fibrillation before randomization are considered dropouts. Patients are randomized by means of a centralized, computer-generated randomization list, with a 1:1 ratio; given that both patients and physicians are aware of the randomized treatment and that patients are specifically trained to manage their symptoms in two different ways depending on the study arm, patients and investigators are not blinded with respect to treatment. At the randomization visit, NYHA class, QoL and atrial and ventricular function are assessed (the latter by echocardiography) in order to evaluate the response to CRT. After randomization, patients are followed up for a total duration of 3 years, with planned ambulatory visits every 6 months.

At follow-up visits a clinical assessment is performed including NYHA class staging, ECG and medical therapy. QoL assessment and echocardiography are mandatory one and two years after randomization. Data regarding events such as hospitalization are collected over the entire follow-up period.

Device shocks and all interventions performed to treat atrial arrhythmias (drug, electrical or other therapy, repeated or not) are collected for both study arms. A protocol for the management of atrial arrhythmias in the traditional arm has not been predefined, but left to center's specific therapeutic practice and decision making, and may range from simple observation of the response to drugs of the hospitalized patient to repeated attempts of internal cardioversion done with the device in a in-hospital environment. The only requirements for this arm are 1) automatic shock set to "off" and 2) arrhythmia treatment performed at in-hospital environment.

If a primary endpoint event, other than patient death, occurs, the patient continues to be followed over the entire 2-year period in order to assess secondary endpoints. Crossover may occur at any point during the follow-up: patients may withdraw from the device-controlled therapy arm when atrial shock therapy is disabled due to severe discomfort related to shocks or too frequent atrial shock therapies; patients may cross from the traditional therapy to the device-controlled arm when atrial shock therapy is enabled chiefly because the number of hospital admissions for atrial cardioversion becomes too frequent. Patients who present with permanent/chronic AF, regardless of the randomization arm, start rate control therapy with the device's atrial therapy set to off: this is not considered a crossover, as the patient has already reached the primary endpoint.

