## Methods/Design

### Study Design and Objectives

The TRADE-HF is a prospective, open-label, randomized, multi-center, two parallel arm study. The study has been approved by the local Ethic Committees of all 20 participating centers and has been registered to http://www.clinicaltrials.gov site (NCT00345592). Enrollment started in November 2006. The steering committee of the study is responsible for the study design and its amendments.

Primary objective of the TRADE-HF study is to demonstrate a reduction in the combination of hospitalizations for cardiovascular causes or death for cardiovascular causes or development of permanent AF, using a device-based treatment of atrial arrhythmias (i.e. automatic therapy) compared to a traditional approach including hospitalization for symptoms and and/or in-hospital treatment of AT/AF (i.e. traditional therapy). Automatic therapy implies that atrial arrhythmias are detected by the device itself which treats the rhythm automatically within 3 hours after episode onset with a predetermined sequence of programmed electrical therapies (anti-tachycardia pacing and electrical shock). On the other side in the traditional arm automatic shock therapy is not active; therefore, patients who will experience symptomatic atrial arrhythmias at home will refer to their center, where treatment of the atrial arrhythmia will be done according to center's practice (e.g. drugs, external cardioversion, device shock commanded by the physician in a hospital environment). Hospitalizations for cardiovascular causes will include any unplanned cardiac cause hospitalization including day hospital, access to the emergency units and in-hospital procedures of AT/AF cardioversion. Permanent AF is considered as any form of AF that is found to be refractory to drug or electrical therapy, for which the physician resigns to take additional actions to restore sinus rhythm and that persists additionally for at least one month. After obtaining informed consent, a three-month observation period ensues, during which the device parameters are optimized, data on atrial arrhythmias are collected and patient's response to the device treatment is assessed. Thereafter, patients are randomized to the two different treatment arms, automatic and traditional therapy in a 1:1 ratio. After being randomized, patients are followed for three years to assess endpoints. The study flowchart is shown in figure 1.

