### Data Analysis

Descriptive statistics will be presented for the collected variables, overall and according to the randomization group; for categorical variables absolute and relative frequencies; for continuous variables mean, standard deviation, median, 25th-75th percentile, minimum and maximum. Baseline characteristics of the two study arms will be listed. Cox modeling will be used to perform the primary analysis and assess the association between treatment (traditional vs. device-managed) and the primary endpoint. Hazard ratios and their 95% confidence intervals will be presented together with Kaplan-Meier cumulative survival and with event rates (per 100 persons per year) in each group. The model will include the following potential confounders: evidence of AT/AF in the patient's medical history or recorded by the device before randomization and patients' response to CRT at randomization. In particular, group effects will be tested by interaction terms comparing the treatment effect in patients who are or are not responders to CRT at randomization. Competing events (causes of death other than cardiovascular, transplant or ventricular assist device implant) will be censored at the time they occur. The primary analysis will be done according to Intention to treat (ITT) i.e. automatic shocks programmed according to randomization. Survival analysis techniques will be used to evaluate time-to-event for the evolution to chronic AF and for both subgroup analyses (CRT responders and AT/AF). In case the primary endpoint is fulfilled, additional post-hoc analyses will be performed. In particular a positive response to CRT responsiveness will be analyzed with respect to the planned variables by means of a logistic regression model. The device's ability to manage and correctly classify atrial arrhythmia will be evaluated considering the sensitivity, specificity and accuracy of the device's classification compared to that made by the Event Committee. Quality of life scores, number and total duration of hospital admissions (for all causes, cardiac causes and for heart failure), total duration of AF and total costs will be compared between the two study arms after 3 years using the appropriate statistical test, according to distribution. For economic analysis costs are estimated for hospitalization (reasons, entry date, duration, department), interventions and instrumental examinations performed. A P value of at least 0.05 will be used for statistical significance.

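### A two-year follow-up statement for patients with a primary event contradicts the three-year follow-up and comparisons elsewhere, and the three-year QoL comparison has no mandated assessment

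*Protocol article*

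**What the plan says.** The protocol article gives the length of follow-up in several places.

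- Study Design and Objectives: "After being randomized, patients are followed for three years to assess endpoints".
- Interventions and Follow Up, general rule: "After randomization, patients are followed up for a total duration of 3 years, with planned ambulatory visits every 6 months". On event data it adds: "Data regarding events such as hospitalization are collected over the entire follow-up period".
- Interventions and Follow Up, on a primary event other than death: "the patient continues to be followed over the entire 2-year period in order to assess secondary endpoints".
- Data Analysis, on the secondary outcomes: "total duration of AF and total costs will be compared between the two study arms after 3 years". The same sentence also covers QoL scores and the number and total duration of hospital admissions.

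On QoL, Interventions and Follow Up says: "QoL assessment and echocardiography are mandatory one and two years after randomization". The items it lists for the routine six-monthly visits are NYHA class, ECG and medical therapy; QoL is not among them. QoL is also assessed at enrollment and at the randomization visit.

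Sample Size assumes a 60% risk of the combined endpoint in the traditional arm, with a three-year horizon, against 43% in the device-managed arm.

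**The concern.** There are two separate discrepancies.

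The first is the length of follow-up. The only sentence that tells sites what to do after a non-fatal primary event gives two years, while every general statement gives three. A site that took that sentence at its word would stop at year 2 in patients who have had an event and continue to year 3 in those who have not. Follow-up length would then depend on the outcome. Because the plan expects more events in the traditional arm, it would also differ by arm. Admissions, days in hospital, AF duration and costs are compared as three-year totals, and a year that was never collected adds nothing to a total. An analysis plan cannot recover data that sites did not collect.

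The second is the QoL time point. QoL is a named secondary outcome to be compared after three years, but the last mandated assessment is at two years. This gap is the same in both arms and does not favour either.

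**Working it through.** **Reproducing the plan's figure.** This confirms that the 60% and 43% risks are the design inputs. For two proportions, the number per arm is

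n = [z(0.975)·√(2·p̄·(1−p̄)) + z(0.90)·√(p1(1−p1) + p2(1−p2))]² / (p1−p2)²

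With p1 = 0.60, p2 = 0.43 and p̄ = 0.515:

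n = [1.960·√0.49955 + 1.2816·√0.4851]² / 0.17² = 5.189 / 0.0289 = 179.5, rounded up to 180 per arm.

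That is the stated 360 in total. The contradiction itself does not depend on the sample size.

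**Sizing the loss if the two-year sentence is applied literally.** Inputs and assumptions:

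- Three-year risks of 60% and 43% (Sample Size). The three-year horizon is stated for the 60% and taken to apply to the 43% as well.
- Constant hazard in each arm (assumption).
- Share of first events that are non-fatal: 70% to 100% (assumption; the article gives no figure). The two-year sentence excludes death, and cardiovascular death is part of the composite.
- Only first events by year 2 are counted. For a first event in year 3 the two-year period is already over.

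Annual hazards are −ln(0.40)/3 = 0.305 and −ln(0.57)/3 = 0.187. The two-year event risks are

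- traditional: 1 − 0.40^(2/3) = 45.7%
- automatic: 1 − 0.57^(2/3) = 31.3%

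| | Traditional | Automatic | Gap |
|---|---|---|---|
| Lose year 3, all first events non-fatal | 45.7% | 31.3% | 14.5 points |
| The same, of 180 per arm | 82 | 56 | 26 |
| The same, of 207 per arm | 95 | 65 | 30 |
| Planned person-time lost (share ÷ 3) | 15.2% | 10.4% | 4.8 points |
| Lose year 3, 70% of first events non-fatal | 32.0% | 21.9% | 10.1 points |

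The last row is 0.70 × 45.7% and 0.70 × 31.3%. Gaps are taken before rounding.

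**If three years applies to everyone,** no year-3 data are lost by design in either arm.

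**Primary analysis.** Data Analysis specifies a Cox model for the primary endpoint. A patient with a non-fatal primary event has already contributed that event, so what is collected afterwards cannot change the result.

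**QoL.** Mandated after randomization: years 1 and 2, in both arms. Time point of the planned comparison: year 3. No arithmetic is needed.

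**The case against.** The strongest reply is that the two-year sentence says the opposite of an early stop. It says that a primary event does not end follow-up and that the patient stays in for the whole period. On this reading, two years is simply a wrong number for the common follow-up length, and no patient is treated differently because of an event. The general statements support this: they give three years for every randomized patient, with no exception for events, and event data are to be collected throughout. A stop at two years would also be hard to apply to a first event in year 3.

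This carries weight. A reader might infer that patients with events are followed for only two years, so that the traditional arm does lose more data. The article does not establish that; the selective loss is conditional on a literal application of one sentence. The reply does not remove the contradiction, however. The wrong number, if that is what it is, stands in the instruction that sites would consult after an event, and nothing in the article says which length prevails.

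Three further points stand.

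- The 45.7% and 31.3% are upper figures under constant hazards, because they treat every first event as non-fatal.
- The QoL schedule is the same in both arms, so it causes no differential loss.
- Mandatory assessments at one and two years set a minimum, and visits continue to year 3. A reader might infer that year-3 QoL data will not exist; the article shows only that none is mandated.

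**Conclusion.** The contradiction is real: one sentence gives two years, while the general follow-up statements and the analysis use three. Its consequence is conditional. Applied literally, the sentence would remove year-3 data only in patients with events: up to 45.7% of the traditional arm against 31.3% of the automatic arm, or about 32% against 22% if 70% of first events are non-fatal. These figures rest on constant hazards, on the planned 60% and 43% risks both holding at three years, and on an assumed non-fatal share. If the expected difference between arms exists, the totals for admissions, AF duration and costs would be understated more in the traditional arm, which biases those comparisons toward no difference. How far each total would shrink cannot be stated, because the article gives no admission rates or dispersion.

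A reader might infer that the trial's main result is at risk. It is not: the primary time-to-first-event analysis and the 360-patient calculation are unaffected.

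The QoL mismatch holds on its own, whichever way the two-year sentence is read, and affects both arms alike. Overall severity is moderate.

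**What to change.** 1. Reconcile the two-year sentence in Interventions and Follow Up with the three-year statements in that section, in Study Design and Objectives and in Data Analysis. One follow-up length should apply to every patient whether or not a primary event has occurred. Tell the sites, preferably before patients with events reach year 2, since year-3 data not collected may be irretrievable. The cost is a clarification: six-monthly visits to year 3 are already planned.

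2. Align the QoL comparison with its schedule. One option is to compare QoL at the mandated one- and two-year assessments, adjusted for the score already collected at the randomization visit. This changes only analysis wording; the downside is that QoL is reported at two years and not three. The alternative is to mandate a year-3 assessment, which adds a questionnaire at a visit already planned.

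Analysing admissions as rates with follow-up time as an offset is not a substitute for the first step. It does not in general remove bias when follow-up ends because of the outcome, and this problem no longer calls for it once follow-up is the same for all.

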### Sample Size

Patients treated for CRT in two large randomized clinical trials, the COMPANION [13] and CARE-HF [14] studies, yielded a respective incidence of 62% and 38% in deaths or hospitalizations due to cardiac reasons after a two-year follow-up period. According to the AFFIRM study [22], the evolution to chronic AF may range between 20% and 25% after two years, in patients who are likely to experience recurrent AT/AF. In HF patients, the prevalence of AF is reported to vary from 10% to 50%, with higher values in older patients and in those with superior NYHA class [23]. Additionally, the incidence of new-onset AF in these patients ranges from 3% and 10% per year [23]. A study of a large cohort of heart failure patients has recently revealed that around one third of hospitalized patients had ECG evidence of AF [24]. Based on these data, we assumed that around 35% of patients in both study arms of the TRADE-HF study will have experienced at least one episode of atrial arrhythmia after three years and that around 60% will have experienced at least one hospitalization for cardiac reasons or persistent/chronic AF or death from cardiovascular causes. Patients treated automatically with the device are expected to have a lower rate of events. The effectiveness of treating AT/AF with a dual-defibrillator is very high and reported to be around 90% in different settings [15,16]. Assuming a 60% risk for combined endpoints in the traditional arm versus a 43% risk in the device-managed arm, using a two-tailed alpha of 0.05, with a Cox proportional hazards regression model the study will need a total of 360 patients (180 per group) in order to achieve a power of 90% and demonstrate a difference in primary endpoint rates among patients in the device-managed arm versus those in the traditional arm. Assuming a 15% attrition rate during the study, due to loss to follow-up or failure to adhere to the study design, the total sample size will amount to 414 patients (207 per group).

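### The 60% to 43% fall behind the 90% power is not derived from the plan's own 35% AT/AF figure, and the plan's figures support it only in a corner case

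*Protocol article*

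**What the plan says.** - **Population.** Patient Selection states that "patients are not selected on the basis of atrial arrhythmia recurrence", apart from excluding chronic or persistent AF. The Discussion confirms enrolment whatever the history of atrial arrhythmia.
- **Expected AT/AF.** For the three-year horizon, Sample Size gives this assumption: "around 35% of patients in both study arms of the TRADE-HF study will have experienced at least one episode of atrial arrhythmia".
- **Effect and size.** The same section continues: "Assuming a 60% risk for combined endpoints in the traditional arm versus a 43% risk in the device-managed arm". The test is two-sided at the 5% level. This gives 360 patients for 90% power, and 414 after an allowance for attrition.
- **Supporting figures.** Sample Size cites 62% and 38% cardiac death or hospitalization at two years in two CRT trials, and about 90% effectiveness of a dual defibrillator in treating AT/AF. It does not show how 43% follows from any of these.
- **Endpoint.** Study Design and Objectives counts emergency-unit visits, day hospital and in-hospital AT/AF cardioversion as primary events, alongside cardiovascular death and permanent AF.
- **Analysis.** Data Analysis puts AT/AF before randomization (history or device record) into the Cox model as a confounder and mentions an AT/AF subgroup analysis. The interaction it specifies is for CRT response: "group effects will be tested by interaction terms comparing the treatment effect in patients who are or are not responders to CRT at randomization".

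**The concern.** The arms differ in how an AT/AF episode is treated. A patient who never has an episode gives the randomized therapy little or nothing to act on, and on the plan's own figure that is about 65% of patients. Their events stay in both arms and pull the overall hazard ratio towards 1. The whole 17-point difference must then come from the other 35%.

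The only efficacy figure offered, about 90%, describes successful treatment of an arrhythmia. It is not a rate of avoiding the composite endpoint. If the true overall fall is much smaller than 17 points, the power is well below 90%, and a neutral result would leave open a substantial effect in patients with AT/AF.

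**Working it through.** **Inputs from Sample Size:** risks 60% and 43%; two-sided alpha 0.05; 360 patients; AT/AF in 35%; background 38% and 62% at two years; device effectiveness about 90%. Allocation is 1:1 (Study Design and Objectives).

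**Assumptions added here:** no treatment effect in patients without an episode; constant hazard when two-year rates are carried to three years; a range for p1, the three-year traditional-arm risk in AT/AF patients, which the plan does not give.

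**Step 1: reproduce the plan.** A pooled two-sided comparison of 60% with 43% at 90% power gives 180 per arm, 360 in total, exactly as stated. On the hazard scale:

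- HR = ln(0.57)/ln(0.40) = 0.613
- Expected events D = 360 × 0.515 = 185
- Power = Φ(|ln HR| × √(D/4) − 1.96) = 91%

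The calculation is sound for the effect put into it.

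**Step 2: the effect needed in AT/AF patients.** Let p0 be the risk without AT/AF (same in both arms) and q1 the device-arm risk with AT/AF.

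- Traditional arm: 0.35 p1 + 0.65 p0 = 0.60
- Device arm: 0.35 q1 + 0.65 p0 = 0.43
- Subtracting: p1 − q1 = 0.17/0.35 = 0.486, about 49 points

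The last column asks a different question: what power 360 patients give if automatic therapy removes all the excess risk of AF, so that the device-arm risk equals p0. It uses the Step 1 power formula.

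| p1 | p0 | q1 needed for 43% | relative reduction needed | power if all AF excess is removed |
|---|---|---|---|---|
| 60% | 60.0% | 11.4% | 81% | no excess to remove |
| 70% | 54.6% | 21.4% | 69% | 19% |
| 80% | 49.2% | 31.4% | 61% | 56% |
| 90% | 43.8% | 41.4% | 54% | 89% |
| 100% | 38.5% | 51.4% | 49% | 99% |

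In the rows up to 90%, the q1 needed is below p0: AT/AF patients on automatic therapy would have to do better than patients with no AT/AF at all.

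**Step 3: when 43% can be reached.** If therapy removes a share f of the AF excess, the overall fall is f × (0.60 − p0).

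- f = 100%: p0 must be at most 43%, so p1 is at least 0.43 + 0.17/0.35 = 92%.
- f = 90%: p0 must be at most 0.60 − 0.17/0.9 = 41.1%, so p1 is at least 0.411 + 0.189/0.35 = 95%.
- At the extreme p1 = 100%, p0 = 38.5% and f must still be 0.17/0.215 = 79%.

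**Step 4: set against the cited background.**

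- 38% at two years becomes 1 − 0.62^1.5 = 51.2% at three. The largest possible fall is 60 − 51.2 = 8.8 points. HR = ln(0.488)/ln(0.40) = 0.783, D = 360 × 0.556 = 200, power 41%. With f = 90% the fall is 7.9 points and power about 34%. Reaching 90% power would take roughly 1,300 to 1,650 patients across these two cases.
- 62% at two years already exceeds the 60% assumed at three years and leaves no AF excess.

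**Step 5: could the 90% figure produce 43%?** Reading it as a 90% reduction of endpoint events in AT/AF patients at 60% risk gives 0.60 × (1 − 0.35 × 0.9) = 41.1%, close to 43%. AT/AF patients in the device arm would then have a risk of 0.60 × 0.10 = 6%, against 60% in patients without AT/AF.

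**Sensitivity.** If 50% of patients had AT/AF, the fall needed in them would be 0.17/0.50 = 34 points (60% to 26% at p1 = 60%).

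**The case against.** **The endpoint ties cardioversion to events.** In-hospital cardioversion and emergency access count as primary events, and the traditional arm must treat arrhythmia in hospital. A treated episode there is itself an event, and a successful automatic shock may avoid it. This stands: it pushes p1 upwards, and at p1 = 90% the plan's power is nearly recovered. A reader might infer that 43% is impossible; the documents do not support that. But the case also needs a three-year background of 43% or less, against a lower cited rate of 38% already at two years. The Discussion adds that asymptomatic episodes may go undetected under the traditional approach, which pulls p1 down.

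**Zero effect without AT/AF is an assumption.** Interventions and Follow Up says that patients are trained to handle symptoms differently by arm, without blinding, so unplanned admissions could differ even without an episode. This stands. The size is unknown, and Sample Size does not rely on it.

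**The cited CRT rates may include AF-related events.** The 51% is therefore approximate.

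**AT/AF is not ignored in the analysis.** It is a covariate and a planned subgroup. Only a named interaction term is absent, and the full protocol or SAP may hold one. The article does, however, specify an interaction, and only for CRT response.

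**A neutral result would still be informative.** A reader might infer that it could not answer the primary objective. That goes too far: the objective compares two strategies in the enrolled population, all-comer enrolment is a deliberate choice, and the overall hazard ratio with its interval addresses that comparison. What it may leave open is the effect within AT/AF patients.

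**Conclusion.** The point holds as a defect in the effect assumption. The stated 90% is right for 60% versus 43%, so a reading that the sample size was miscalculated from those inputs would be wrong. What lacks support is the 17-point fall in all patients when only about 35% are expected to have an episode. It needs about 49 points in those patients. Even with full removal of AF excess, it also needs a traditional-arm AT/AF risk of about 92% or more and a background of 43% or less.

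Under full removal, power with 360 patients is about 19%, 56% and 89% at AT/AF control risks of 70%, 80% and 90%. It is about 41% at the lower cited background. These figures rest on no effect outside AT/AF episodes, constant hazard and an assumed p1. They show how far the power depends on quantities the plan leaves unstated; they do not predict the trial's true power.

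**What to change.** **Sample Size.** Derive the device-arm risk from the 35%. State the three-year control risk with and without AT/AF, the effect assumed in AT/AF patients, and any effect expected without an episode. Replace the single 90% with power over that range, such as the 19%, 56% and 89% above, and reconcile the chosen background with the cited 38% and 62% at two years.

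**Data Analysis.** Add a treatment-by-AT/AF interaction using the pre-randomization covariate already in the model. Report the treatment effect on the primary endpoint in patients with that covariate as a supportive estimate. State that a neutral overall result does not exclude an effect in AT/AF patients.

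**Cost.** Amended wording and one model term; no extra patients and no change to randomization. The stated power becomes less favourable, and the fix describes the power honestly without raising it. The subgroup estimate is less precise than the overall one (35% of 360 would be only 126 patients). The covariate also does not define the same group as the 35%: it misses AF that first appears after randomization, which the Discussion gives as a reason for all-comer enrolment.

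### The 15% attrition allowance is computed as 360 × 1.15 = 414 instead of 360/0.85 = 424, and it replaces non-adherers by headcount although the ITT analysis keeps them

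*Protocol article*

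**What the plan says.** The Sample Size section of the protocol article sets the effect as follows: "Assuming a 60% risk for combined endpoints in the traditional arm versus a 43% risk in the device-managed arm". It continues "using a two-tailed alpha of 0.05, with a Cox proportional hazards regression model", and states that "the study will need a total of 360 patients (180 per group) in order to achieve a power of 90" percent.

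The allowance comes next: "Assuming a 15% attrition rate during the study, due to loss to follow-up or failure to adhere to the study design". Loss and non-adherence share this one figure, with no split between them. The conclusion that the section draws from it is that "the total sample size will amount to 414 patients (207 per group").

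The Data Analysis section then says: "The primary analysis will be done according to Intention to treat (ITT"). The Interventions and Follow Up section permits crossover in both directions during follow-up and gives no expected rate. The 60% and 43% risks are not adjusted for it.

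**The concern.** There are two separate difficulties.

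- **Arithmetic.** Adding 15% of the pre-attrition number does not offset a 15% loss from the enrolled number. The stated total therefore does not keep the 360 that the calculation calls for.
- **Consistency with the analysis.** A patient lost to follow-up takes information away, and recruiting more patients replaces it. A patient who stops following the allocated strategy is still analysed in the allocated arm under ITT and pulls the two arms together. Extra recruitment does not restore the effect size. The allowance treats both groups alike.

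What is at stake is how the 90% can be read. If the result is neutral, a reader will set it against the claimed power, and the article does not say how much non-adherence that claim can absorb.

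**Working it through.** **Inputs.** Risks of 60% and 43%, two-sided alpha 0.05, 90% power, 360 patients, 15% attrition and 414 patients (Sample Size); 1:1 allocation and three years of follow-up (Study Design and Objectives); ITT (Data Analysis). Mean event risk = (0.60 + 0.43)/2 = 0.515.

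**1. Reproducing 360.**

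- Two-proportion test with pooled variance and no continuity correction: n = [1.96·√(2·0.515·0.485) + 1.2816·√(0.60·0.40 + 0.43·0.57)]² / 0.17² = 179.5, so 180 per group and 360 in total. This matches exactly.
- Proportional hazards: HR = ln(0.57)/ln(0.40) = 0.613.
- Freedman: (1.96 + 1.2816)²·[(1 + HR)/(1 − HR)]² = 183.1, so 184 events; 184/0.515 = 358 patients. This is within 1% of 360.
- Schoenfeld: 4·(1.96 + 1.2816)²/(ln HR)² = 176.04, so 177 events. Dividing by 0.515 gives 342 (unrounded events) to 344 (rounded) patients.

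**2. The inflation.**

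- 360 × 1.15 = 414, the stated total.
- 414 × 0.85 = 351.9, about 352 left.
- 360/0.85 = 423.5, so 424 (212 per group): 10 more patients, or 2.4%.

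**3. Power at 352, with the risks unchanged.** Two-proportion 89.4%, Freedman 89.7%, Schoenfeld 90.8%. These figures assume that lost patients contribute nothing. A Cox analysis uses their time until censoring. If all 15% were lost uniformly over three years (an assumption), about 199 events are expected and Schoenfeld power is 93.2%.

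**4. ITT dilution, N = 414.** Assumptions: a fraction *a* of the device arm is non-adherent, the remaining 15% − *a* of each arm is lost and contributes nothing, and the traditional arm adheres.

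- Switch on day 0: device-arm risk = 0.43(1 − a) + 0.60a.
- Switch at mid-follow-up with constant hazards: a switcher's three-year risk is 1 − √(0.57 × 0.40) = 0.5225, so device-arm risk = 0.43(1 − a) + 0.5225a.

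Power is shown from the two-proportion test to Schoenfeld.

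| Non-adherent + lost | Device-arm risk, day 0 | Power, day 0 | Device-arm risk, mid-follow-up | Power, mid-follow-up |
|---|---|---|---|---|
| 5% + 10% | 43.85% | 88.0–89.5% | 43.5% | 89.5–90.9% |
| 10% + 5% | 44.7% | 86.2–87.9% | 43.9% | 89.4–90.8% |
| 15% + 0% | 45.55% | 84.0–85.8% | 44.4% | 89.2–90.6% |

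Using 424 instead of 414 in the day-0 scenarios adds less than one percentage point. Correcting the inflation therefore does not deal with dilution.

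**The case against.** The strongest reply is that the plan still has about the power it claims. At 352 patients the Schoenfeld figure is 90.8%. On Schoenfeld's own requirement, correct inflation gives 344/0.85 = 405, fewer than 414. Patients lost part-way still contribute to a Cox model. Failure to adhere to the design need not mean treatment crossover, which the article describes separately. Device-arm patients leave because of shock discomfort or shock frequency, hence after some time on therapy, so the day-0 assumption is severe. All of this stands, and it limits the size of the point. It does not make 414 the right inflation of 360, and it does not reconcile a headcount allowance for non-adherence with an ITT analysis.

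Four stronger readings are tempting, and the documents support none of them:

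- **That 90% power is not delivered.** The article gives no split of the 15% and no crossover rate. If the 15% is all loss, power is about 89.4% to 93.2%, depending on the formula and the censoring.
- **That 360 cannot come from a proportional-hazards calculation.** Freedman's formula gives about 358. The exact match with two proportions does not show which formula was used.
- **That equal crossover in both arms cuts power to roughly 68% to 86%.** Crossover out of the traditional arm is chiefly for frequent cardioversion admissions. Those already count as primary endpoint events, so most such crossover follows the first event and barely affects a time-to-first-event analysis.
- **That the missing event target is a defect.** Patients have a fixed three-year follow-up after randomization, so the design is not presented as event-driven. Monitoring against 177 events would be a preference.

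**Conclusion.** The point holds in two parts.

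First, the stated total is arithmetically wrong for its purpose: 414 leaves about 352, and 424 is needed to keep 360. The consequence is minor, about 0.6 to 0.7 percentage points compared with power at 360, which leaves 89.4% to 90.8% even if lost patients contribute nothing.

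Second, non-adherence is handled as removable loss although the primary analysis retains those patients. How much power this costs cannot be fixed from the article. For 5% to 15% device-arm non-adherence within the 15%, it is about 84% to 89.5% with the control risk from day 0, and about 89% to 91% with a switch at mid-follow-up. These ranges rest on assumed splits, assumed timing, constant hazards for the mid-follow-up case, and an adherent traditional arm.

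The supportable conclusion is that the 90% is not justified by the calculation shown once non-adherers are retained. It has not been shown to be unattainable.

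**What to change.** Revise the Sample Size text in three places:

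1. Correct the inflation to 424 (212 per group), or keep 414 and state that 15% attrition leaves about 352 evaluable, with power of about 89% to 91% before any dilution.
2. Separate loss to follow-up from non-adherence. Give the ITT power with non-adherers retained, under a stated crossover rate and timing.
3. Name the formula behind 360. It matches a two-proportion test exactly and Freedman within 1%; Schoenfeld gives 342 to 344.

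The change is to text only. If 414 is kept and its power restated, no further patients are needed; choosing 424 means recruiting 10 more. The downside is a stated power that may look slightly less favourable.
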